### Adverse event of special interest

Not applicable.

### Pregnancy reporting

Pregnancy is not considered an AE. However, if pregnancy is confirmed during the treatment period, the study intervention will be discontinued, but participants may continue to be followed up.

The timeline for reporting pregnancy events is the same as that for SAEs, and follow-up should continue until the pregnancy outcome (e.g., termination of pregnancy, childbirth). Investigators are required to report pregnancy events to the sponsor within the specified timeframe.

If subsequent events occur during pregnancy, they should be managed as SAEs: fetal/neonatal congenital abnormalities or deformities, spontaneous abortion, termination of pregnancy for medical reasons.

Both male and female participants should take effective contraceptive measures after enrolling in the study.

## Unanticipated problem (UP)

### Definition of unanticipated problem (UP)

The risks to participants or others arising from UP must be carefully evaluated. Generally, these include any event, process, or outcome that meets all of the following criteria:

1. **Unexpected:** The event is unexpected in terms of its nature, severity, or frequency, given: (a) the research procedures described in the protocol-related documents, such as the study protocol approved by the Institutional Review Board (IRB) and the informed consent form; and (b) the characteristics of the population being studied.
2. **Related or possibly related:** The event is related or possibly related to participation in the research ("Possibly related" means that there is a reasonable possibility that the event, process, or outcome was caused by procedures involved in the study).
3. **Greater risk of harm:** The event suggests that participants or others may be at greater risk of harm than was previously known or recognized (including physical, psychological, economic, or social harm).

### UPs reporting

Investigators will report UPs to the IRB reviewers and the Principal Investigator (PI). UP reports will include the following information:

1. **Protocol identification information:** Protocol name and number, PI name, and IRB project number.
2. **Detailed description of the UP:** A detailed description of the event, including any associated circumstances or outcomes.
3. **Basis for identifying the UP:** A description of how the event, associated circumstances, or outcomes were identified as a UP.
4. **Description of any protocol changes or corrective actions:** A description of any changes to the protocol or other corrective actions that have been taken or proposed in response to the UP.

To meet the need for prompt reporting, UPs will be reported according to the following schedule:

1.**UPs related to SAEs**: UPs related to SAEs will be reported to the IRB and the study sponsor within 24 hours of the investigator becoming aware of the event.

2.**Any Other UPs**: Any other UPs will be reported to the IRB and the study sponsor within 24 hours of the investigator becoming aware of the event.

3.**Reporting to regulatory authorities:** Within 24 hours of receiving a report of a problem from the investigator, the IRB should report all UPs to the provincial, autonomous region, or municipal drug administration authorities and the Drug Adverse Reaction Evaluation Center.

### Suspected unexpected serious adverse event (SUSAR) reporting

Suspected Unexpected Serious Adverse Reaction (SUSAR) refers to a serious adverse event that is suspected and unexpected, based on the nature and severity of the clinical presentation exceeding the information documented in the Investigator's Brochure for the investigational drug, the package insert for marketed drugs, or the Summary of Product Characteristics. It is an AE that meets the criteria of being related, serious, and unexpected. The term "unexpected" means that for an investigational drug, the event is not listed in the Investigator's Brochure, Package Insert, or Summary of Product Characteristics, or its nature and severity go beyond what is described in the Investigator's Brochure.

1. The sponsor is responsible for reporting SUSARs to all participating trial sites and ethics committees. For unexpected serious adverse reactions that are fatal or life-threatening, the sponsor must report them within 7 days of first becoming aware of the event and submit follow-up information within the subsequent 8 days. For non-fatal or non-life-threatening unexpected serious adverse reactions, the sponsor must report them within 15 days of first becoming aware of the event. The day the sponsor becomes aware of the event is considered Day 0.
2. If the trial sites and ethics committees can directly accept SUSAR reports from the sponsor, the sponsor must deliver one copy of the SUSAR report to the trial sites and ethics committees within the specified timeframe, and another copy, after being reviewed and signed by the investigator, must be submitted again to the trial sites and ethics committees.
3. If the trial sites and ethics committees only accept SUSAR reports reviewed by the investigator, the sponsor's delivery of the SUSAR and the investigator's review and sign-off must meet the regulatory timelines required for reporting to the trial sites and ethics committees.
4. When the sponsor and investigator cannot reach consensus on the causal relationship between the unexpected serious adverse event and the investig drugational, if either party cannot rule out a relationship with the investigational medication, the event should be reported promptly. The sponsor must rapidly report the SUSAR to all investigators and trial centers participating in the clinical trial, as well as to the ethics committees, drug regulatory authorities, and health administration departments.

### Reporting UPs to participants

### After the occurrence of an UP, proactive measures should be taken. Following the investigator's assessment of the relevance, timely communication with the patient is necessary to seek patient’s opinion on whether to continue participating in the study and receiving the intervention.

1. Statistical Analysis

## Analytical set

### Modified intention-to-treat (mITT) set/full analysis set (FAS)

### All subjects who are included in the mITT/FAS have received randomization and have at least two post-baseline efficacy assessments, regardless of whether they completed the entire treatment.

### Safety set (SS)

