| Study population | Screening population: 248  Number of patients to be included in the study: 210 (105 per study arm).  The actual number of patients included: 210 (108 in the perospirone group and 102 in the placebo group)  Number drop outs: 43 (23 in the perospirone group and 20 in the placebo group)  Number of patients to be evaluated: 177 in mITT (FAS) evaluation (87 in the perospirone group and 90 in the placebo group), and 167 with complete follow-up (85 in the perospirone group and 82 in the placebo group) |
| Inclusion criteria | - Meeting Diagnostic and Statistical Manual of Mental Disorders, Fifth Edition (DSM-5) criteria for MDD, confirmed by the Mini International Neuropsychiatric Interview (MINI); - The current episode duration of MDD must be ≤1 year; - Failed to respond adequately to at least one kind of antidepressant at therapeutic doses for at least 4 weeks, as indicated by a current score of at least 20 on the Montgomery-Asberg Depression Rating Scale (MADRS); - Aged 18 ~ 60 years; - Education >= 6 years and able to complete the cognitive tests; - Having the ability to understand and sign a written informed consent form prior to participation in any screening procedures. |

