| Exclusion criteria | - Any other DSM-5 psychiatric disorder other than generalized anxiety disorder and social anxiety disorder diagnosed at present or lifetime; - Subjects with serious suicide ideation or attempts; - Subjects who have received treatments with adjunctive antidepressants and/or antipsychotic medications in the current depressive episode (small doses of benzodiazepines were permitted); - Subjects who have received non-drug treatments in past 6 months for more than 10 times, such as electroconvulsive therapy (ECT), repetitive transcranial magnetic stimulation (rTMS), and systemic psychotherapy; - DSM-5 alcohol or drug dependence; - History of head injury or loss of consciousness for more than 5 minutes; - Subjects with a history or current diagnose of major physical illness (such as thyroid disease, lupus erythematosus, diabetes, lung, liver and kidney damage, infection, major trauma and etc.); - Pregnant or breast-feeding; - Epilepsy, history of seizures or family history of epilepsy; - Receiving hormone therapy at present; - Transaminases (ALT or AST) 2 times or more above the upper limit of normal range; - QTc >= 430 msec (for males) or >= 450 msec (for females) in ECG; - Any subject with some other conditions that the researchers believe may affect the study results. |
| Study visits | Visits will be conducted at 0 weeks ± 2 days, 2 weeks ± 2 days, 4 weeks ± 2 days, and 8 weeks ± 2 days after enrollment in the trial. |
| Efficacy end points | Primary efficacy end points:   - MADRS response rate (defined as an improvement of ≥50% in the MADRS score from baseline) at week 4 and week 8. - MADRS remission rate (defined as a MADRS score of ≤10) at week 4 and week 8.   Secondary efficacy end points:   - Reduction rates in MADRS and Hamilton Anxiety Scale (HAMA) scores at each visit. - Change rates in each Clinical Global Impression (CGI) and Beck Suicidal Ideation Scale (BSI-CV) subscales scores at each visit. - Reduction rates in Pittsburgh Sleep Quality Index (PSQI), 16-item Quick Inventory of Depressive Symtomatology-Self-Report (QIDS-SR16), Generalized Anxiety Disorder 7-item Scale (GAD-7), and Snaith-Hamilton Pleasure Scale (SHAPS) scores at each visit. - Change rates in Sheehan Disability Scale (SDS) and Quality of Life Enjoyment Questionnaire - Short Form (Q-LES-Q-SF) scores at each visit. - Change rates in neurocognitive function test performance before and after treatment. |

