For the primary efficacy outcomes and partial secondary efficacy outcomes (i.e. response and remission rates at weeks 4 and weeks 8), last observation carried forward (LOCF) method was used to handle the missing data in the anaysis of these outcomes. Since these outcomes were defined based on MADRS scores at the corresponding visit (response: ≥50% reduction from baseline; remission: MADRS score ≤10), missing MADRS values in the FAS were imputed using LOCF, and response or remission status was subsequently determined based on the imputed scores. Logistic regression models were employed to analyze and compare these outcomes between the the perospirone + SSRIs/SNRIs group (perospirone group) and the placebo + SSRIs/SNRIs group (placebo group), using results of the placebo group as reference. In the logistic regression model, treatment group was included as factor, and baseline MADRS total score was included as a covariate.

For the other secondary efficacy measures, the mean change of the included scales (MADRS, QIDS-SR16, HAMA, and Q-LES-Q-SF) from the baseline (Week 0) to Week 4 and Week 8 were analyzed. The mean changes and the differences of the mean changes of the secondary efficacy outcomes between the perospirone group and the placebo group were calculated and compared through the use of a mixed model for repeated measures (MMRM) analysis (with an unstructured covariance matrix). This method is widely recommended for longitudinal data with missing values under the missing at random (MAR) assumption, as it utilizes all available data and does not require explicit imputation. The model included the baseline total scores of each scales, study centre (centre 1 to centre 10), treatment group (perospirone and placebo), time (week 2, week 4 and week 8), and time-by-treatment interaction as fixed effects, with the subjects-specific effects as a random effect. The least squares mean (LSM) changes of the scores for the two groups were reported.

Chi-square tests or Fisher’s precision probability tests were conducted to compare the overall incidence rates of AEs, SAEs and AEs leading to treatment discontinuation, as welll as the incidence rates of each drug related-AE between the two groups. All statistical analyses were done in Statistical Analysis System (SAS) version 9.4. Statistical significance was determined by a two-sided p value less than 0.05

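### The mITT/FAS requires two of the three post-baseline assessments, so the primary analysis drops 33 of 210 randomised patients on post-randomisation attendance (21 perospirone, 12 placebo), which is likely, but not shown, to favour perospirone

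*Protocol*

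**What the plan says.** Section 9.1.1 of the protocol treats the mITT set and the FAS as one set, made up of subjects who "have received randomization and have at least two post-baseline efficacy assessments, regardless of whether they completed the entire treatment". Section 9.2.2 and section 12, item 5, run the efficacy analyses in that set. Section 9.2.4 also mentions a per-protocol set. No analysis of all randomised patients is stated.

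The visit schedule in section 1.1 reads "Visits will be conducted at 0 weeks ± 2 days, 2 weeks ± 2 days, 4 weeks ± 2 days, and 8 weeks ± 2 days", which gives three post-baseline visits.

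Within the FAS, section 12, item 5, fills missing MADRS values by LOCF and then derives response and remission. For the scale scores it prefers an MMRM, with week 2 as one of its time points, "as it utilizes all available data and does not require explicit imputation".

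The synopsis (section 1.1, study population) reports the actual counts:
- randomised: "210 (108 in the perospirone group and 102 in the placebo group)"
- drop-outs: "43 (23 in the perospirone group and 20 in the placebo group)"
- analysed: "177 in mITT (FAS) evaluation (87 in the perospirone group and 90 in the placebo group)"
- completed: "167 with complete follow-up (85 in the perospirone group and 82 in the placebo group)"

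**The concern.** A full analysis set should keep the groups that randomisation created. This rule selects patients on something that happens afterwards. With three post-baseline visits, two assessments normally means staying to about week 4. The label mITT suggests a minor departure from intention to treat, but the set is close to a completer set.

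The rule also conflicts with the protocol's own methods. LOCF needs only one post-baseline MADRS, and the MMRM is chosen because it uses every available observation, yet a patient with one post-baseline visit contributes to neither. Elsewhere the entry rules are looser: the safety set needs one dose (section 9.1.2) and the TESS comparison needs one follow-up visit (section 9.2.3).

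Both primary endpoints are at stake. If early leavers do worse than those who stay, and more of them are removed from one arm, the estimate shifts towards that arm.

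**Working it through.** **Inputs.** Randomised 108/102, FAS 87/90, drop-outs 23/20 and completers 85/82 (perospirone/placebo, section 1.1). Planning rates are 46.6% vs 26.6% for response and 36.8% vs 18.9% for remission (section 12, item 3). The response rate of the excluded patients is not in the document, so it is varied below.

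**Do the protocol's figures agree?**
- Completers: 108 − 23 = 85 and 102 − 20 = 82, as stated. Completers meet the two-assessment rule, so every excluded patient is a drop-out.
- Sample size, unpooled formula: n = (1.960 + 0.842)² × (0.466×0.534 + 0.266×0.734) / 0.200² = 87.1, so 88 per group. Inflated for 10% drop-out: 176/0.9 = 195.6, so 196. Both match section 12, item 3.

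**Who is excluded**
- Perospirone: 108 − 87 = 21 (19.4%). Placebo: 102 − 90 = 12 (11.8%). Total: 33/210 (15.7%).
- Difference: 7.7 points, 95% CI −2.1 to 17.4, Fisher p = 0.13.
- Share of drop-outs removed: 21/23 = 91% vs 12/20 = 60%, Fisher p = 0.028.
- Drop-outs still in the FAS, on whom LOCF can act: 87 − 85 = 2 perospirone and 90 − 82 = 8 placebo.
- Completers in the FAS: 167/177 = 94%.

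**Effect on the response difference.** Suppose the planning rates hold among FAS patients, and let e₁ and e₂ be the response rates of the excluded patients. Over all randomised:

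D = (87×0.466 + 21e₁)/108 − (90×0.266 + 12e₂)/102

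| Assumption for the excluded | Perospirone | Placebo | D (points) |
|---|---|---|---|
| None respond | 37.5% | 23.5% | 14.1 |
| Respond at the placebo rate (26.6%) | 42.7% | 26.6% | 16.1 |
| Respond at half their own arm's rate | 42.1% | 25.0% | 17.0 |
| Respond like their own arm | 46.6% | 26.6% | 20.0 |
| All respond | 57.0% | 35.2% | 21.7 |

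With one common rate e in both arms, D = 14.1 + 7.7e points. This reaches 20.0 at e ≈ 0.77. Below that rate the FAS favours perospirone, and above it the bias runs the other way. The extremes, with all excluded patients in one arm responding and none in the other, are 2.3 and 33.5 points. For remission the 17.9-point planning difference becomes 13.0 with the excluded as non-remitters.

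**Effect on the test** (illustrations, not trial results; Pearson chi-square)
- Near the planning rates: 41/87 vs 24/90 gives 20.5 points, p = 0.005. With the excluded as non-responders, 41/108 vs 24/102 gives 14.4 points, p = 0.024.
- A borderline case chosen to show sensitivity: 48/87 vs 36/90 has p = 0.043, and 48/108 vs 36/102 has p = 0.18.
- No true difference, 35% response in both arms over all randomised: if no excluded patient responds, the FAS rates are 0.35×108/87 = 43.4% and 0.35×102/90 = 39.7%, and a two-sided 5% test rejects 8.2% of the time. If the excluded respond at half the common rate, rejection is 5.8%. At the full common rate it is 5.0%.

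**The case against.** A reader might infer that the rule demonstrably biases the trial in favour of perospirone. The document does not support that. It gives neither reasons nor outcomes for the 33 excluded patients. Sections 7.2 and 7.3 list adverse events and disease progression as grounds for leaving, but also the participant's own wish, poor compliance, newly found ineligibility and loss to follow-up. The imbalance in exclusions is compatible with chance (p = 0.13). The sharper contrast among drop-outs (p = 0.028) is a post-hoc comparison of 43 people. The bias vanishes if the excluded would have responded like their own arm, and it reverses if most would have responded.

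The largest effects also rest on counting every excluded patient as a non-responder. Even then, a result near the planning rates stays significant, and the example that loses significance was picked at the margin.

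The MMRM inconsistency cannot be sized. The document does not say how many of the 33 had one post-baseline visit and how many had none, and those with none would add no post-baseline data to the model.

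All of this stands, and it limits what can be said about direction and size. It does not rescue the rule: selecting the primary set on attendance departs from intention to treat whatever the direction, and a per-protocol analysis would not repair it.

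**Conclusion.** The point holds in limited form. The rule is stated outright, it governs both primary endpoints, and the protocol's own counts show that it removes 15.7% of randomised patients, unevenly by arm. That it favours perospirone is likely, not shown. It would follow if fewer than about 77% of the excluded would have responded (a common rate in both arms, planning rates in the FAS). It would not follow if they would have responded like their own arm.

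On those planning rates, a 20-point FAS difference corresponds to about 14 points with the excluded as non-responders and 16 to 17 under the milder assumptions. These figures use all 108 and 102 randomised patients. The number who took at least one dose is not given, so the effect of a dosed-patients set cannot be computed. Confidence is high on the rule and the counts, and moderate on direction.

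**What to change.** In section 9.1.1, define the primary efficacy set as all randomised patients, or all randomised patients who took at least one dose, with a baseline MADRS and no minimum number of post-baseline visits.

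In section 9.2.2 and section 12, item 5, state how a missing week-8 status is assigned. LOCF has no post-baseline value to carry for a patient with no post-baseline MADRS, so that case needs its own rule, for example non-responder in the primary analysis with multiple imputation as a sensitivity analysis.

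Report the current 177-patient set as supplementary. The protocol already gives actual enrolment and describes its adjustments in the past tense. If the primary set can no longer be changed, report the all-randomised analysis alongside it and label it as added later. Give the reasons for exclusion of the 33 patients by arm, and how many had one or no post-baseline assessment.

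The cost is one definition, one imputation rule and a re-run. The estimate will probably be less favourable to perospirone.

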### All subjects who received at least one dose of the study drug after enrollment will be included in the safety analysis.

## Statistical analyse

### Sample size calculation

### Accroding to the results from the previous study on the perospirone combination therapy for patients with MDD, the response rate of the experimental group was approximately 78%~90%, and that of the placebo group was about 47%~71%. The maximum response rates of the two groups were used for the estimation of the sample size. Using Power Analysis and Sample Size Software 8.0, we conducted chi-square test to determine that a sample size of 174 participants (87 per group) would provide 80% power (β = 0.2) at a two-sided alpha level of 0.05 (α = 0.05) to detect a significant between-group difference in the primary efficacy outcome. Considering a 20% dropout rate, the final sample size was adjusted to 210 participants (105 per group).

### Efficacy end points analyse

### To make the results of the statistical analysis more precise, efficacy analyses are performed in the FAS. Missing data in the FAS will be imputed with the last-observation-carried-forward (LOCF) approach.

### Efficacy end points including:

**A.Primary efficacy end points:**

1. MADRS response rate: the proportion of participants with a ≥50% reduction in the MADRS score from baseline at week 4 and week 8.

2. MADRS remission rate: The proportion of participants with an MADRS score ≤10.

**B.Secondary efficacy end points:**

1. .Reduction rates in MADRS and Hamilton Anxiety Scale (HAMA) scores at each visit.

2. Change rates in each Clinical Global Impression (CGI) and Beck Suicidal Ideation Scale (BSI-CV) subscales scores at each visit.

3. Reduction rates in Pittsburgh Sleep Quality Index (PSQI), 16-item Quick Inventory of Depressive Symtomatology-Self-Report (QIDS-SR16), Generalized Anxiety Disorder 7-item Scale (GAD-7), and Snaith-Hamilton Pleasure Scale (SHAPS) scores at each visit.

4. Change rates in Sheehan Disability Scale (SDS) and Quality of Life Enjoyment Questionnaire - Short Form (Q-LES-Q-SF) scores at each visit.

5. Change rates in neurocognitive function test performance before and after treatment.

### Safety end points analyses

The safety set (SS), included of individuals who have received at least one dose of the randomized investigational drug, were employed to analyze the safety and tolerability profile of the medication by comparing the self-reported AEs/SAEs of the two groups of patients. Since the AEs covered by the TESS involve multiple systems, which could assess the safety of the drug in a more comprehensive manner. Therefore, the TESS was also used for safety evaluation. Nevertheless, since the TESS set to be completed by patients during follow-up visits, on the basis of the SS sample, those with at least one follow-up visit were included for inter-group comparisons of the incidence of AEs based on the TESS. For TESS items, a score of 0 indicates that the patient did not experience the corresponding AE. Conversely, any score greater than 0 signified that the patient experienced the AE during the treatment period.

